## Abstract

Balneotherapy (BT) is considered an effective, non-pharmacological approach, in the multimodal treatment of the Primary Fibromyalgia Syndrome (FS). However, the evidence of efficacy and tolerability of BT in FS is still limited. This is a prospective multi-center two-cohort observational study. The main aim will be the comparison of the Minimal Clinically Important Difference (according to Fibromyalgia Impact Questionnaire—FIQ) achievement in FS patients treated with BT vs standard care. Secondary objectives will be to assess: a) BT impact on pain, quality of life, anxiety and depression; b) the persistence of benefits in six weeks c) BT safety profile. All FS patients with a stable treatment in the past 3 months and a moderate to severe disease (FIQ score ≥ 39) will be enrolled after providing written informed consent. Patients will be divided into two Cohort: a) BT Cohort (i.e., BT in addition to standard care)—BTC; b) Control Cohort (i.e., only standard care)—SCC. There will be three assessments: baseline, two and six weeks (i.e., one month after BT end in BTC). At each of them the subject will fill in the following questionnaires: FIQ, VAS pain, Short Form Health Survey 16, State-Trait Anxiety Inventory and Center for Epidemiological Studies Depression Scale. We expect to observe a more relevant improvement of disease activity in BTC than in SCC. The positive effect may extend even to pain, quality of life, anxiety and depression. The short- and medium-term effects are likely to be similar, without any significant warning in terms of tolerability. Collected data, deriving from a large sample of patients, will provide a new insight of BT role in moderate to severe FS treatment. In particular, it will be possible to quantify the short and medium-term BT impact on disease activity and secondary symptoms related to FS.

## Introduction

Fibromyalgia Syndrome (FS) is a long-lasting condition, characterized by the ongoing presence of widespread musculoskeletal pain, fatigue, sleep disruptions, headaches, irritable bowel syndrome, as well as anxiety and depression (Mease 2005; Sarzi-Puttini et al. 2020). It affects between 1 and 5% of the general population, with women being six times more likely to be diagnosed than men (Giorgi et al. 2023). FS significantly impacts patients’ quality of life (Häuser et al. 2018). Pain and functional impairments often result in work absenteeism, frequent medical consultations, and the pursuit of various conventional or alternative treatments, leading to substantial direct and indirect healthcare costs (Spaeth 2009; Vervoort et al. 2016).

Despite advancements in understanding its pathophysiology, there are still no specific pharmacological treatments for FS. Current international guidelines recommend a multidisciplinary and multimodal approach, combining both pharmacological and non-pharmacological therapies (Macfarlane et al. 2016).

Balneotherapy (BT) includes a wide array of therapeutic methods such as hydrotherapy, bathing in mineral-rich water, mud therapy, or utilizing natural remedies, typically performed in health spas (Gutenbrunner et al. 2010; Vaccarezza and Vitale 2010; Fioravanti et al. 2017; Antonelli et al. 2021). In 2002, the World Health Organization (WHO) categorized BT within traditional or complementary medicine, acknowledging its broad therapeutic applications (WHO 2002). Furthermore, the European League Against Rheumatism (EULAR) and the Italian Society of Rheumatology (SIR) endorse BT as a valid treatment option within the multimodal management of FS (Macfarlane et al. 2016; Ariani et al. 2021).

Several meta-analyses, systematic reviews, randomized controlled trials, and observational studies confirm the efficacy and tolerability of BT in managing FS (Fioravanti et al. 2007; Naumann and Sadaghiani 2014; Cao et al. 2021; Maindet et al. 2021; Ducamp et al. 2022; Colas et al. 2024; García-López et al. 2024). However, there are limited studies that focus on the effects of BT on pain, functional symptoms, health-related quality of life, anxiety, and depression in a large group of patients with moderate to severe FS. We hypothesize that combining BT with standard treatment is both safe and more effective than standard treatment alone in managing FS patients.

The primary aim of this study will be to evaluate whether BT increases the proportion of patients achieving the Minimal Clinically Important Difference (MCID) as measured by the Fibromyalgia Impact Questionnaire (FIQ), compared to standard care. Secondary aims will be a) the assessment of BT additional effects on pain, quality of life, anxiety and depression, b) the persistence of clinical efficacy over a six-week follow-up, c) the tolerability of BT by recording all adverse events, their severity and possible relationship with the therapy.

## Methods

### Study design and ethics

FIBROTHERM is a prospective multi-center, two-cohort observational study. The enrollment period will take place from April 2023 to November 2024 (deadline for the enrollment of the last patient) by the centers participating in the study. From June 2025, the data will be analyzed and then, disseminated. The estimated total duration of the study will be 26 months.

The study will be conducted in accordance with the “Declaration of Helsinki (1964) and following amendments. All eligible patients will provide a written informed consent, and this will be recorded in the appropriate outpatient file. The study protocol was approved by the Ethics Committee of the Area Vasta Sud Est-Toscana (Italy) on March 2023; the same document was submitted and approved by local Ethics Committees of the other participating centers to ensure that all local regulatory requirements were met. Furthermore, the study was registered on http://www.clinicaltrials.gov: NCT05801497.

### Participants

#### Inclusion criteria

Patients of both sexes meeting the 2016 American College of Rheumatology (ACR) criteria for primary FS (Wolfe et al. 2016) and aged between 18 and 75 years will be eligible for this study. Indeed, for this study we will include patients with a FIQ score ≥ 39 (i.e. moderate to severe disease) and receiving stable pharmacological and non-pharmacological treatment over the previous three months.

#### Exclusion criteria

Exclusion criteria will include: 1) enrollment in other research protocols in the 6 months before the study begins; 2) BT treatment in the last 6 months; 3) intra- or extra-articular steroid injections in the previous 3 months; 4) pregnancy or breastfeeding; 5) presence of cognitive disorders, psychiatric illnesses and/or drug addictions (including alcohol) that can hinder the administration of the questionnaires; 6) absolute or relative contraindications to BT as reported in the literature (Fioravanti and Marcolongo 2000).

### Settings of the enrollment and where the data were collected

Patients with primary FS will be enrolled in the Rheumatology or Rehabilitation Units of public general Hospitals and public University Hospitals. Currently, nine centers, located throughout Italy, have joined the FIBROTHERM study. The same centers will be responsible for clinical data collection.

### Interventions and study arms

This study consists of two parallel cohorts:BT Cohort (BTC): Patients will receive a cycle of bath or of mud-bath therapy once daily for 12 days in addition to their usual treatments for FS (see below). The thermal treatment cycle will include one session per day for a total of two weeks, with a break between the fifth and seventh day to prevent the onset of a thermal crisis. This protocol aligns with current practices and is endorsed by the Italian National Health Service which covers a cycle of a 12-day treatments, once a year for patients with rheumatic diseases such as FS. The mineral thermal baths will be carried out in a single tub or in a pool, with a duration of 10 min at a temperature of 37–38° C. The thermal mud will be applied to the skin according to standardized methods, with a duration of 15–20 min, at temperatures ranging between 40–45° C. A rest period of about 20–30 min will follow BT treatment. The whole treatment duration will last 1 h, approximately. Only muds and baths belonging to the classes of sulfurous, bicarbonate, chloride-sodium, sulphate and arsenical-ferruginous waters—according to the classification of Marotta and Sica (1933), will be allowed.Control Cohort (SCC): This group will include patients who will refuse the BT for personal reasons. Patients will continue their established routinely care for FS.

The usual care treatment will correspond to pharmacological and non-pharmacological therapies as reported in EULAR guidelines (Macfarlane et al. 2016). The intervention program must have already been stabilized for at least 3 months before the start of the study. During the study period, the patient can modify the therapy if necessary; this change will be reported.

### Outcomes

#### Primary outcome

The primary outcome of the study will be the percentage of patients with a minimal clinically important difference (MCID), defined as a decrease of more than 14% in their FIQ-Total score, at 15 days (Bennett et al. 2009; García-López et al. 2024).

The FIQ is a self-administered questionnaire evaluating the impact of the disease in daily activities; the score ranges from 0 to 100, and higher scores indicate a greater impact of the disease (Table 1). A score lower than 39 is considered a mild impact, 39 to 59 is considered moderate, and greater than 59 is considered severe (Burckhardt et al. 1991). In the present study, we will use the Italian translated validated version (Sarzi-Puttini et al. 2003).

**Table 1 Tab1:** Description of tests which will be administrated

Test	Description
Fibromyalgia Impact Questionnaire (FIQ)	FIQ is a self-administered instrument composed of 10 items that measure fibromyalgia patient status, progress and outcomes. Each question is rated on a 4-point Likert-type scale
Visual Analogue Scale (VAS)	Unidimensional measure of patients’ pain intensity, used to record pain progression and compare pain severity between patients
Widespread Pain Index (WPI)	19-point checklist that assesses the presence of pain or tenderness in 19 specific areas of the body; each affected area receives one point
Short-Form Health Survey (SF-12)	Self-reported outcome measure assessing the impact of health on an individual's everyday life. It is often used as a quality of life measure
State-Trait Anxiety Inventory (STAI)	STAI is a test that measures two types of anxiety – state anxiety and trait anxiety. It consists of 40 self-report items on a 4-point Likert scale, with higher scores representing higher levels of anxiety
Centre for Epidemiologic Studies Depression Scale (CES-D)	Brief self-report questionnaire developed to measure depressive symptoms severity. The CES-D consists of 20 questions that ask about various symptoms of depression as they have occurred in the past week

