### Sample size

The primary outcome is the modification of the FIQ total score, whose minimum clinically relevant difference is 14% as compared to its initial value (Burckhardt et al. 1991). We expect a decrease in the FIQ total score of at least 14% in the 30% of the control cohort and 45% in the BT cohort. A number of 217 patients per group allows estimating an absolute difference of 15% (45—30%) in the incidence of the primary outcome between the two cohorts at an alpha level = 0.05 and with a power of 90% (Pearson’s chi-squared test). Assuming a loss to follow-up of 20%, 260 (217 + 43) patients will be enrolled per group, for a total of 520 patients.

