#### Secondary outcomes

The secondary outcomes of the study will be the differences in VAS, SF-12, STAI, and CES-D between the BT and control cohorts. These differences will be evaluated using a random effects linear regression model (RE-LRM) (Rabe-Hesketh and Skrondal 2021) 39. The response variable of such models will be the (continuous) score obtained from the scale and the predictors will be: 1) time (discrete; 0 = baseline; 1 = 15 days), 2) the cohort (discrete; 0 = control cohort and 1 = BT cohort), and 3) a time*cohort (discrete*discrete) interaction, with the random effect assigned to the patient. A Bonferroni correction will be used to correct the 95% confidence intervals and associated p-values. As already described for the BRM used for the evaluation of the primary outcome, also the RE-LRM will be expanded to a multivariable model by adding predictors (= potential confounders) determined preliminarily with the clinicians participating in the study. Interactions initially determined or suggested by the multivariable analysis may also be included among the predictors. An univariable selection of the predictors will not be carried out, but predictors will be progressively added to the model to verify the effect on the estimate of the difference in the scores for the BT and control cohort (Greenland and Pearce 2015).

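### FIQ total is analysed only as a >14% responder, so the plan yields no between-cohort difference in FIQ points and no between-cohort FIQ estimate at 45 days

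*Protocol article*

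**What the plan says.** Under Outcomes, Primary outcome, the endpoint is "the percentage of patients with a minimal clinically important difference (MCID), defined as a decrease of more than 14% in their FIQ-Total score", assessed at 15 days. The same section describes FIQ as running from 0 to 100. The Abstract and the Follow up section have it collected at baseline, 2 weeks and about 6 weeks (45 days).

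Under Statistical analysis plan, Primary outcome, four FIQ analyses are set out: a chi-square test, a univariable binomial model, a multivariable binomial or Poisson model, and a binomial model comparing 15 with 45 days. The response is the >14% reduction throughout. The last model is confined to the BT cohort and is meant to check whether the change in FIQ total is stable.

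Under Statistical analysis plan, Secondary outcomes: "The secondary outcomes of the study will be the differences in VAS, SF-12, STAI, and CES-D" between cohorts. These get a random-effects linear model of the score with time, cohort and their interaction. Time has two levels, baseline and 15 days.

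The Abstract states that "it will be possible to quantify the short and medium-term BT impact on disease activity". The Sample size section opens with "The primary outcome is the modification of the FIQ total score" but then sizes the study on responder proportions.

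**The concern.** The main instrument is handled with less detail than the four scales listed for the score model. Two things that a reader of the results would want are missing.

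- **Size in points.** The cut is relative to baseline, so the same responder status means different absolute changes: 0.14 × 39 = 5.5 points at the entry threshold and 0.14 × 100 = 14 points at the top of the scale. The control cohort consists of patients who decline BT, so baseline FIQ may differ between cohorts. A score model would show baseline and change side by side; a responder proportion does not.
- **A medium-term contrast.** At 45 days the only FIQ model is within the BT cohort. Without controls, it cannot separate persistence of benefit from the course that untreated patients would also follow. A responder proportion can also stay level while the mean score drifts, so that model is a weak check on stability of the score.

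A dichotomised score is usually less precise than the score itself. That loss is avoidable in a secondary analysis, because the data are collected anyway.

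**Working it through.** **Which FIQ estimates the plan yields**

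| | Responder (>14%) | FIQ score |
|---|---|---|
| Between cohorts, 15 days | risk difference, relative risk, 95% CI | none |
| Between cohorts, 45 days | none | none |
| Within BT cohort, 15 vs 45 days | binomial model | none |

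WPI, named as a secondary outcome under Pain, is also absent from the score model, so FIQ is not the only scale left out.

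**The plan's own figure**

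Inputs from the Sample size section: "at least 14% in the 30% of the control cohort and 45% in the BT cohort", and "at an alpha level = 0.05 and with a power of 90% (Pearson’s chi-squared test". Two-sided alpha is assumed, as sidedness is not stated; mean proportion 0.375.

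n = [1.960·√(2·0.375·0.625) + 1.282·√(0.30·0.70 + 0.45·0.55)]² / 0.15²
= [1.3419 + 0.8668]² / 0.0225 = 216.8, so 217. This matches "A number of 217 patients per group", and power at 217 is 90.0%.

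**What the same effect implies for a comparison of means**

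The documents give no FIQ SD or distribution. Assume first that percent change is normal with equal SDs.

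- Shift: d = z(0.45) − z(0.30) = −0.1257 + 0.5244 = 0.399 SD.
- n for 90% power = 2·(1.960 + 1.282)² / 0.399² = 132.2, so 133 per cohort.
- Ratio: 133/217 = 0.61, a loss of about 39%.
- Power of the means comparison at 217 = Φ(0.3987·√(217/2) − 1.960) = Φ(2.193) = 98.6%.

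**Range under other assumptions**

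Logistic distribution: the log odds ratio is ln(0.45/0.55) − ln(0.30/0.70) = 0.6466. In SD units, 0.6466·√3/π = 0.357, which gives n = 166 and a loss of 1 − 166/217 = 24%.

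Normal with BT SD equal to k times control SD: d = 0.5244 − 0.1257k in control SDs, and n = (1.960 + 1.282)²·(1 + k²)/d².

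| k | d | n per cohort | Loss against 217 |
|---|---|---|---|
| 0.75 | 0.430 | 89 | 59% |
| 1.00 | 0.399 | 133 | 39% |
| 1.25 | 0.367 | 200 | 8% |
| 1.33 | 0.357 | 228 | none (means comparison needs 5% more) |

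All of these concern percent change, because the cut is 14% of the baseline value. The score model uses the raw FIQ total, so they indicate what the cut may cost and are not power figures for that model.

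**The case against.** The strongest case against is that the responder endpoint is legitimate, matches the primary aim at the end of the Introduction, and is properly sized. Four points follow, and the first three stand.

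- A reader might infer that the study cannot quantify the effect on disease activity. The documents do not support that. The plan commits to absolute and relative risk changes with 95% confidence intervals at 15 days, marginal percentages in each cohort, and an adjusted relative risk. The abstract does not promise a mean difference in points.
- A reader might take "The primary outcome is the modification of the FIQ total score" as a promise of a score analysis. Its sentence goes on to the 14% criterion, and the calculation that follows targets "an absolute difference of 15% (45—30%) in the incidence of the primary outcome between the two cohorts". This is loose wording.
- A reader might quote 39% as the established loss, or conclude that the study is larger than it needs to be. The figure rests on an assumption that the documents neither state nor support. A larger SD in the BT cohort is plausible if response to BT varies between patients, and it would shrink or remove the gain.
- The article condenses a fuller protocol, and a supplementary summary of FIQ scores might sit there. This carries less weight. The article contains its own analysis plan, which names the response variable of each FIQ model and lists the outcomes for the score model. The gap is in what that plan states.

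**Conclusion.** The point holds as an analysis omission, not as a flaw in the design or the primary endpoint. As written, the plan produces no between-cohort difference in FIQ points at any time and no between-cohort FIQ estimate at 45 days. The second gap is the more serious, because it leaves the medium-term half of the abstract's statement without a comparison against standard care. Neither gap depends on a distributional assumption.

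The precision argument is secondary. The loss from the cut is about 39% under equal-SD normality, 24% under a logistic distribution, and 59% to 8% for BT/control SD ratios of 0.75 to 1.25; it is gone by a ratio of 1.33. The direction favours the score over most of that range, but the size is unknown. The change is worth making and easily made, and the study's main conclusion does not hang on it.

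**What to change.** - Keep the responder primary endpoint and the sample size.
- Add FIQ total score as the first-listed secondary outcome in the random-effects time-by-cohort model, with time levels baseline, 15 and 45 days. Report the confounder-adjusted difference in mean change between cohorts, with 95% CI, at both follow-up times.
- Reword the opening of the Sample size section so that the primary outcome is the proportion with a FIQ decrease of more than 14% at 15 days, as under Outcomes. The same edit can remove the mismatch between at least 14% there and more than 14% elsewhere.

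The data are already to be collected at all three visits, so the cost is one more model and one more outcome in the Bonferroni-corrected secondary family. If that family is counted by scale, for example, the per-outcome level moves from 0.05/4 = 0.0125 to 0.05/5 = 0.01. If it is counted by contrast, the two FIQ time points add two.

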#### Secondary outcomes

##### Pain

Pain intensity will be evaluated by a Visual Analogue Scale (VAS), a 10-cm long line with the value 0 on the left indicating “no pain” and the value 10 on the right indicating the “worst imaginable pain” (Scott and Huskisson 1976).

Furthermore, we will consider as a secondary outcome, the Widespread Pain Index (WPI) that is a measure of the number of painful areas (score range = 0–19) on the patient’s body over the last week before the assessment (Wolfe et al. 2010).

##### Quality of life

The quality of life will be assessed by the Short-Form Health Survey (SF-12), a short version of SF-36 that is a widely used measure of health and well-being, validated in multiple countries, including Italy (Ware et al. 1996; Apolone and Mosconi 1998).

SF-12 includes two main domains: the physical component score (PCS) and the mental component score (MCS), and eight scales for assessing eight dimensions: physical functioning, physical role, social role, emotional role, bodily pain, general health, vitality, and mental health. Scores range from 0 to 100 where 0 indicates the worst condition and 100 indicates the best possible condition.

##### Anxiety

The anxiety will be evaluated by the State-Trait Anxiety Inventory (STAI): this a self-administered test with two independent scales (STAI T-Anxiety Scale or Form X-2 and STAI S-Anxiety Scale or Form X-1); each one includes 20 items. A high score on the STAI corresponds to a high level of anxiety symptoms. For the present study, we will use the Italian validated STAI (Spielberger et al. 1983; Lazzari and Pancheri 1980).

##### Depression

The assessment of depression will be performed by the Italian validated version of Centre for Epidemiological Studies Depression Scale (CES-D) (Radloff 1977; Fava 1983). It is a self-administered 20 items questionnaire evaluating the frequency of depression symptoms in the previous week; scores range from 0 to 60, with high scores indicating greater depressive symptoms. Scores of 16 or above are considered at risk for clinical depression.

##### Tolerability

All adverse events, whether reported spontaneously by the patients or observed by the physician, will be reported in the personal record noting the severity. The adverse event will be considered related to the treatment if it appears after the start of the therapy or if it was known as a BT side effect. In addition, side effects related to drug therapy will be monitored and reported as part of the study.

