### Follow up

Following enrollment, each patient will be examined for 3 consecutive times; at baseline (T0), after 2 weeks (T1), and after 45 days (T2) (one month after the end of the cycle of the therapy for the BT Cohort) (Fig. 1). T0 and T1 visits will be carried out by the physician in the enrollment setting. The T2 visit will be carried-out by phone. The study will be considered concluded when all follow-up data for each patient will be collected.

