BT also offers significant mental health benefits, particularly in reducing anxiety and depressive symptoms common in FS. Its anti-inflammatory effects may influence brain chemistry, as inflammation is linked to mood disorders like depression (Fioravanti et al. 2024, Koroglu and Yıldız 2024). Notably, IL-6, an inflammatory marker, is associated with sleep disturbances, and BT’s ability to regulate IL-6 could be a key mechanism behind its positive effects on sleep quality. In addition, warm, mineral-rich water promotes relaxation and reduces stress, contributing to better sleep patterns (Antonelli et al. 2024a, 2024b). This restorative sleep further enhances the benefits of BT by reducing fatigue and improving psychological resilience, ultimately leading to better overall well-being (Moini Jazani et al. 2023; Manica et al. 2024).

Furthermore, we expect to confirm a good tolerability of BT in a large sample of patients with moderate-severe FS.

In conclusion, the favorable effect of BT extended to several domains, including quality of life, anxiety and depression, could be particularly useful in the multimodal treatment of this disease.

A notable strength of this study is its large sample size and the involvement of nine specialized public facilities across Italy, which ensures a comprehensive representation of the national context.

Moreover, the results of this study have the potential to provide valuable insights that could help shape best practices for the clinical management of FS. Additionally, it may offer new evidence to further validate the role of BT as part of the complex approach to treating FS.

Nevertheless, there are some limitations to consider. Firstly, the observational nature of the study is a key limitation. Secondly, there will be no standardization of the BT treatments, as different mineral waters and specific protocols will be employed at each center, which is consistent with a real-world study design. Similarly, the routine care for FS, including both pharmacological and non-pharmacological treatments, will not be standardized but will follow the recommendations provided by the EULAR guidelines (Macfarlane et al. 2016).

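### Adverse event capture as described is passive and unequal between cohorts, and the planned FIQ analyses do not separate patients who worsen from those unchanged

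*Protocol article*

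**What the plan says.** The Introduction sets as secondary aim (c) "the tolerability of BT by recording all adverse events, their severity and possible relationship with the therapy". The Tolerability section gives the method: "All adverse events, whether reported spontaneously by the patients or observed by the physician, will be reported in the personal record noting the severity". It then treats an event as "considered related to the treatment if it appears after the start of the therapy or if it was known as a BT side effect", and adds that "side effects related to drug therapy will be monitored and reported as part of the study". It describes no question put to all patients.

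Under Follow up, "T0 and T1 visits will be carried out by the physician in the enrollment setting", and "The T2 visit will be carried-out by phone". Under Interventions and study arms, the BT cohort has 12 daily treatments with a break, planned so as to prevent a thermal crisis. The control cohort continues usual care.

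The primary outcome is the proportion of patients with an MCID, "defined as a decrease of more than 14% in their FIQ-Total score, at 15 days". The 45-day FIQ analysis, in the BT cohort only, uses the same responder definition. The secondary analysis section models VAS, SF-12, STAI and CES-D as continuous scores and does not list FIQ. According to the Abstract, FIQ is completed at all three assessments.

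The Discussion states an expectation: "we expect to confirm a good tolerability of BT in a large sample of patients with moderate-severe FS".

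**The concern.** There are two gaps, and they meet at the same question: could this study show harm if there were any?

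The first is ascertainment. The aim is to record all events, but the routes named are what patients volunteer and what a physician happens to observe. Little can be observed by phone, so events after T1 depend almost wholly on the patient raising them. During the treatment fortnight the BT cohort has daily attendances and the control cohort has none, so the chance that an event enters the record differs by cohort. A comparison of event rates would then mix tolerability with opportunity to report.

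The second is deterioration. A one-sided responder outcome puts a patient whose FIQ rises clearly into the same class as one whose FIQ does not move. With no other FIQ analysis planned, a gain in responders could sit alongside more patients made worse, and the FIQ results would not show it.

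**Working it through.** **The plan's own figure.** The only design calculation is the sample size for the primary outcome. With 30% against 45%, two-sided alpha 0.05 and 90% power:

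n = [1.960 × √(2 × 0.375 × 0.625) + 1.282 × √(0.30 × 0.70 + 0.45 × 0.55)]² / 0.15² = 216.8, so 217 per group.

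This reproduces the stated 217. It has no bearing on tolerability, for which the article gives no event rate, capture rate or threshold. What follows is therefore illustration. The inputs from the document are the 260 enrolled per group, the 20% loss, and the 30% and 45% responder rates. All other rates are assumptions.

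**1. Incomplete capture.** Let true incidence be 1% (assumed) and let s be the fraction of events that reach the record (assumed). Then P(at least one recorded) = 1 − (1 − 0.01 × s)^n.

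| s | n = 260 | n = 208 (260 × 0.80) |
|---|---|---|
| 1 | 0.927 | 0.876 |
| 0.5 | 0.728 | 0.647 |
| 0.25 | 0.478 | 0.406 |

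For commoner events, the expected recorded count in 260 patients is 260 × rate × s. At a 10% true rate it is 26, 13 and 6.5 for s = 1, 0.5 and 0.25.

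**2. Unequal capture.** Suppose the true rate is 10% in both cohorts of 260 (assumed).
- Capture 50% in BT and 25% in control: 13 against 6.5 recorded, an apparent ratio of 2.
- Capture 25% in BT and 50% in control: 6.5 against 13, an apparent ratio of 0.5.

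The same truth gives opposite answers. The article does not say which pattern would apply. It does not state who supervises the sessions or whether reactions there are passed to the study physician.

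**3. Deterioration.** Keep the plan's 45% and 30% improved and vary the share who worsen by more than 14% (assumed).

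| | BT improved / worsened | Control improved / worsened | Primary difference | Net difference |
|---|---|---|---|---|
| A | 45% / 5% | 30% / 5% | 15 points | (45 − 5) − (30 − 5) = 15 points |
| B | 45% / 20% | 30% / 5% | 15 points | (45 − 20) − (30 − 5) = 0 points |

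The primary result is identical in A and B. The net difference weights improvement and worsening equally, which is itself an assumption. It serves only to show that the planned FIQ outputs cannot tell the two apart.

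**The case against.** A reader might infer that passive capture is the sole route, that BT harms will be under-recorded, and that the method therefore favours a finding of good tolerability. The documents do not support that reading, for four reasons.

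- The sentence on capture names sources and does not exclude enquiry at visits. An article may leave the adverse event form to the full protocol, so silence about a question does not prove that none exists. What remains is that the routes the article chose to state are both passive.
- The direction is open. The relatedness rule counts any event after the start of therapy as related, which over-attributes events to BT. The 12 sessions also give the BT cohort more occasions for an event to be seen or mentioned. Both work against a favourable result. Over-attribution cannot, however, recover events that were never recorded, so the two problems do not cancel.
- Good tolerability is an expectation in the Discussion, with no test or threshold attached. It is not a conclusion that the plan has built in.
- FIQ is a disease-impact score, and a worse score is not an adverse event. Patients who worsen already count as failures, and broad deterioration would pull down the modelled differences in VAS, SF-12, STAI and CES-D. That is correct, but mean differences do not show how many patients got worse.

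There is also a practical objection. Enrolment was planned to end in November 2024, so a new question may come too late for many or all contacts and cannot be applied retrospectively. This stands, and it shapes the fix.

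**Conclusion.** The point holds in a limited form. As described, adverse event capture is passive, with one in-person contact after baseline and a phone contact at T2, and the opportunity to record events differs between the cohorts. Counts are likely to be incomplete and should not be read as comparable between cohorts, in a direction that the documents leave open. The planned FIQ analyses also cannot separate deterioration from no change, although the data to do so are collected.

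The size is not known. The drop from 93% to 48% in the chance of recording a 1% event, and the net difference of 15 points against 0, rest on assumed incidence, reporting and worsening rates and are illustrative only. The primary comparison is not affected. What is at stake is whether aim (c) can be answered in a way that could contradict the stated expectation.

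**What to change.** - **Adverse events.** In addition to spontaneous reports, ask every patient in both cohorts the same non-leading question at T1 and T2, for example whether there has been any new or worse symptom or medical problem since the last contact. Record onset date and severity. If the full protocol already provides for this, say so in the Tolerability section.
- **Contacts already completed.** Report which capture method applied to which contacts, and add passive capture to the limitations in the Discussion, which do not mention it now.
- **Deterioration.** Report by cohort the proportion with an FIQ-Total increase of more than 14% at T1 and at T2, labelled as deterioration and kept apart from adverse events. Because the scale ends at 100, such a rise is impossible from a baseline above 100 / 1.14 = 87.7, so state how many patients in each cohort start above that value.

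The cost is one question at two contacts that already take place and one table from data already collected. The downsides are more minor events on record, a less favourable-looking event rate, and two capture methods within one study if the question is introduced midway.
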